## Abstract

**Background:**

Obsessive Compulsive Disorder (OCD) is a distressing and debilitating condition affecting 1-2% of the population. Exposure and response prevention (ERP) is a behaviour therapy for OCD with the strongest evidence for effectiveness of any psychological therapy for the condition. Even so, only about half of people offered ERP show recovery after the therapy. An important reason for ERP failure is that about 25% of people drop out early, and even for those who continue with the therapy, many do not regularly engage in ERP tasks, an essential element of ERP. A mindfulness-based approach has the potential to reduce drop-out from ERP and to improve ERP task engagement with an emphasis on accepting difficult thoughts, feelings and bodily sessions and on becoming more aware of urges, rather than automatically acting on them.

**Methods/Design:**

This is a pilot randomised controlled trial of mindfulness-based ERP (MB-ERP) with the aim of establishing parameters for a definitive trial. Forty participants diagnosed with OCD will be allocated at random to a 10-session ERP group or to a 10-session MB-ERP group. Primary outcomes are OCD symptom severity and therapy engagement. Secondary outcomes are depressive symptom severity, wellbeing and obsessive-compulsive beliefs. A semi-structured interview with participants will guide understanding of change processes.

**Discussion:**

Findings from this pilot study will inform future research in this area, and if effect sizes on primary outcomes are in favour of MB-ERP in comparison to ERP, funding for a definitive trial will be sought.

**Trial registration:**

Current Controlled Trials registration number ISRCTN52684820. Registered on 30 January 2014.

## Background

Obsessive compulsive disorder (OCD) is a distressing and debilitating mental health condition affecting approximately 1 to 2% of the population [1,2]. People with OCD experience unpleasant, repetitive, unwanted and intrusive thoughts (for example, thoughts of harm coming to a loved one) and engage in compulsive behaviours that are meaningfully related to the thought in terms of preventing harm (for example, repeated checking or cleaning) or that are intended to reduce anxiety.

The behavioural theory of OCD draws on behavioural theory of anxiety disorders more broadly and suggests that compulsive behaviours are maintained through the process of negative reinforcement. That is, compulsive behaviours result in the temporary relief of anxiety, and therefore, these behaviours are reinforced, becoming more likely to occur in the future [3]. This theory informed behavioural therapy for OCD: Exposure and Response Prevention (ERP) [4]. The therapy encourages people to gradually and regularly expose themselves to triggers of their intrusive thoughts (for example, touching surfaces perceived as ‘contaminated’) whilst not engaging in their usual compulsive behaviours (for example, hand washing). Although ERP was developed in the 1960s [4], it is still the form of psychological therapy for OCD with the most robust evidence of effectiveness. Consequently, national treatment guidelines in the UK recommend ERP as *the* psychological therapy for OCD [2]. The guidelines recommend either individual or group-based ERP, and there is randomised controlled trial evidence that group ERP is effective [5] and that individually delivered cognitive behavioural therapy for OCD is not more effective than when delivered in a group [6].

Despite the success of ERP, there are substantial limitations. Only about half of people with OCD meet recovery criteria after a course of ERP [7]. Primarily, this seems to be because many people find ERP too challenging; by definition, the therapy involves intentionally and regularly exposing oneself to anxiety-provoking situations and disengaging from efforts to eliminate anxiety. Twenty-five percent of people drop out of therapy early [8]. Moreover, people with OCD show poor distress tolerance [9] and are therefore particularly likely to find it difficult to engage in exposure-based therapies. Even among those who do complete a course of ERP, many do not fully engage with the regular between-session exposure and response prevention tasks [10], with lower rates of task engagement being associated with poorer therapy outcomes [10]. Therefore, there is a real need to find ways of making ERP more acceptable to patients in order to reduce drop-out rates and increase engagement with exposure tasks. Increasing patient engagement in this way will hopefully lead to a greater number of patients meeting recovery criteria upon completion of an ERP course of treatment.

Mindfulness is a state of awareness characterised by non-judgemental, accepting attention towards current experiences, such as thoughts, feelings and bodily sensations. Training in mindfulness has been incorporated into mindfulness-based interventions (MBIs) in recent years [11,12]. There is increasing evidence that MBIs have positive consequences for psychological [13,14] and physical [15] health, in a broad range of mental health [16-18] and nonclinical [19,20] populations.

Despite this wealth of literature, there is a paucity of research of MBIs for OCD [21]. However, a mindfulness-based approach might be expected to enhance engagement with ERP for three reasons. First, exposure during ERP elicits intrusive thoughts that the person would typically attempt to eliminate by engaging in compulsive behaviours. It has long been established that intrusive thoughts are common throughout the general population and are not usually problematic [22]. Mindfulness-based interventions teach people to allow such thoughts into awareness without attempting to suppress them and to attend to them non-judgementally [12]. Therefore, a mindfulness-based approach to ERP would be expected to enable people to be better able to accept the intrusive thoughts elicited following exposure to triggering situations and to remain engaged in the ERP task despite these thoughts. Second, it is also well established that people with OCD show a heightened intolerance of anxiety [9]. Just as with thoughts, MBIs teach people to notice and accept unpleasant physical sensations and anxiety and to disengage from attempts to avoid or eliminate them [12]. It would be expected, therefore, that a mindfulness-based approach would help people to attend to and accept the physical sensations of anxiety that come about during ERP tasks and to, nevertheless, remain engaged with the tasks. Third, MBIs encourage people to notice the range of behavioural choices they can make in response to an event, rather than reacting to such events automatically [12]. A mindfulness-based approach to ERP should, therefore, support people to better recognise their urges to engage in compulsive behaviours and to make the choice to resist these urges during ERP tasks. Mindfulness-based interventions are usually offered in groups, and ERP can be offered either individually or in groups [2]; thus, a group approach to integrating MBI with ERP is warranted.

A group of six people, all with lived experience of OCD who had experience of ERP and mindfulness-based approaches, were consulted when developing this protocol. The group advised that an integrated mindfulness-based ERP group would be more likely to improve symptom outcomes and to enhance engagement in comparison to either type of intervention (that is, MBI or ERP) on its own. In light of this advice and the background literature outlined above, we expect that a mindfulness-based approach to group ERP would be more effective and have lower rates of drop-out than group ERP on its own.

Given the lack of research in this area to date [21], this is a protocol for a pilot randomised controlled trial (RCT). The research question for the definitive trial is as follows: ‘Is group mindfulness-based ERP more effective at reducing OCD symptom severity and better at enhancing therapy engagement than standard group ERP for people diagnosed with OCD?’ The primary aim of this pilot study is to estimate the size and direction of the treatment effect, and the corresponding 95% confidence interval, by comparing mindfulness-based ERP (MB-ERP) groups to standard exposure and response prevention (ERP) groups on the primary outcome measures of OCD symptom severity and therapy engagement. If the magnitude of these effects are deemed clinically relevant, then the estimate will be used in a power calculation for the definitive trial. Secondary aims of the definitive study will be to test effects on other important outcome (depression and wellbeing) and process (mindfulness and obsessive-compulsive beliefs) measures and so these measures are included in the pilot study to assess their feasibility. In addition, the pilot study will gather information on rates of recruitment and will record rates of attrition from the study. A semi-structured interview with participants will also be conducted to ascertain experiences of change and attributions for change from participants’ perspectives. Information from these interviews will inform the development of future research in this area.

## Methods/Design

### Design and sample size

This is a pilot study for a single blind, prospective RCT using an intention-to-treat comparison of two treatment groups (MB-ERP and ERP). Measures will be taken at baseline (Time 1), post-therapy (Time 2) and at 6 months post-therapy (Time 3). A power calculation to determine sample size is not appropriate for this pilot study [23,24], as there is no intention to identify a statistically significant difference between the two treatment groups. This study follows recommendations for pilot RCTs [25] and aims to have at least 12 participants per treatment arm who provide full data. We aim to recruit 40 people with OCD to allow up to 40% attrition from the study, which is a conservative estimate of what might be expected to occur in ERP [8].

This study has received full ethical approval through the South East Coast (Surrey) arm of the National Research Ethics System in the UK (Research Ethics Committee reference: 13/LO/1768).

### Participants

Participants will be 40 adults referred to a mental health trust in the South of the England. Inclusion criteria are that participants (1) meet DSM-IV [26] diagnostic criteria for OCD; (2) have been stable on psychiatric medication for at least 3 months prior to the consent meeting; (3) have no plans for changes to psychiatric medication during the course of the study; (4) have not received psychological therapy in the past three months or have any plans for psychological therapy during the course of the study; and (5) are older than 18 18 years of age. Exclusion criteria are as follows: those who have an identified organic cause for their OCD symptoms, a diagnosed learning disability, or if they meet the diagnostic criteria, based on the Mini International Neuropsychiatric Interview (MINI version 6.0.0) [27], for a psychotic disorder, post-traumatic stress disorder, anorexia nervosa, alcohol abuse or substance abuse (non-alcohol). This will be ascertained through the care team. To reflect the reality of mental health services and the comorbidity of OCD with other mental health conditions [2], comorbidity will not be an exclusion criterion. People presenting with hoarding-only compulsions will be excluded from the study, given the recent move to classify hoarding as distinct from OCD [1].

### Measures

#### Diagnostic status

*Mini International Neuropsychiatric Interview* (*MINI version 6.0.0*) [27]. DSM-IV OCD diagnostic criteria [26] will be established at all three time points using the Mini International Neuropsychiatric Interview. Meeting diagnostic criteria at baseline is an inclusion criterion for the study.

##### Exposure and response prevention engagement

Engagement will be measured in two ways: (1) the number of therapy sessions attended (maximum = 10) will be recorded, and (2) participants will be asked to record in a daily diary the number of ERP tasks performed each day.

#### Secondary outcome measures

*Short Warwick-Edinburgh Mental Well-Being Scale* [29]. The short version of the Warwick-Edinburgh Mental Well-Being Scale is a 7-item measure of well-being. Stewart-Brown and colleagues [30] reported strong internal consistency, test re-test reliability, and concurrent validity and found that the measure is sensitive to change in mental health populations.

*Beck Depression Inventory - second edition (BDI-II)* [31]. Depression is often comorbid with OCD, with depression thought to arise as the secondary condition [2]. The BDI-II is one of the most widely used measures of depressive symptoms. Beck and colleague [31] reported excellent internal consistency and test re-test reliability (α >0.9 for both). Concurrent validity with the Hamilton Psychiatric Rating Scale for Depression-Revised is also good (r = 0.71).

*Five-Facet Mindfulness Questionnaire - Short Form (FFMQ-SF)* [32]. The FFMQ-SF is a 24-item self-report scale assessing five mindfulness facets: observing, describing, acting with awareness, non-judgement and non-reacting. The short form has been reported to have adequate indices of reliability (α > .73 for each subscale) and validity [32].

*Obsessional Beliefs Questionnaire - Revised (OBQ-44)* [33]. The OBQ-44 is a 44-item self-report measure of cognitions associated with OCD. The instrument has three subscales: (1) Responsibility/Threat Estimation, (2) Perfectionism/Certainty, and (3) Importance/Control of thoughts. The scales have excellent internal consistency (α > .89 for each subscale), and the total score on the OBQ-44 distinguishes between people diagnosed with OCD and non-OCD anxious controls [33].

*Change Interview* [34]. The Change Interview is a semi-structured questionnaire designed to ask participants their experiences of a psychological intervention. Specifically, it asks about changes that have occurred in the person’s life since starting the intervention and to what they attribute these changes. Changes can be attributed to the intervention or to other factors. Finally, participants are asked to comment on the aspects of the intervention that helped change to occur and those aspects that might have hindered change from occurring.

### Procedure

Figure 1 shows the flow of participants through the pilot RCT. Patients with a diagnosis of OCD will be sought through mental health teams in the host NHS trust. Informed consent will be obtained from each participant. Potential participants will be given a copy of the study participant information sheet and will have the opportunity to discuss the study in person with the research assistant (RA) before signing the consent form. The study research assistant will conduct the baseline assessments of consenting participants on the above measures within four weeks of the groups starting. After baseline assessments have been completed, participants will be randomly allocated to either an MB-ERP or an ERP group by a Clinical Trials Unit using block randomisation. Ten participants will be allocated to each group so that there will be two MB-ERP groups and two ERP groups in total. Ten therapy sessions for each group will be facilitated by two clinical psychologists, at least one of whom will be an accredited Cognitive Behavioural Therapy (CBT) therapist and an accredited mindfulness-based cognitive therapy teacher. Sessions will be held either in NHS premises or suitable community venues. Post-group assessments on each of the outcome measures will be conducted by a second RA who will be blind to group allocation.

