#### Mindfulness-based exposure and response groups

The MB-ERP group will be provided with 10 sessions of mindfulness-based behaviour therapy (ERP), each session lasting two hours. Session 1 will introduce the rationale for ERP alongside the rationale for including mindfulness principles and practice. Sessions 2 to 9 will each start with a 10-minute mindfulness practice: mindfulness of the breath and body (session 1); mindfulness of the breath, body, sounds and thoughts (sessions 2-3); mindfulness of thoughts (session 4-5); and mindfulness of body, thoughts, urges and action (sessions 6-10). Mindfulness practice will be followed by a 20-minute Socratic inquiry about the practices in order to draw out learning, with a particular emphasis on the three areas noted above: non-judgmental acceptance of (intrusive) thoughts, non-judgmental acceptance of physical sensations (of anxiety) and a recognition that it is possible to choose whether or not to follow behavioural urges (to engage in compulsive behaviours). A three-minute mindfulness breathing space practice [12] will also be introduced from session 6 onwards for participants to use on a daily basis to bring awareness to current experiences and to facilitate engagement in ERP tasks. In session 1, participants will be given an MP3 player with the range of mindfulness practices for daily home practice, with practice being recorded in the daily diary. The final 90 minutes of MB-ERP session will follow the same ERP protocol outlined above with the addition that whilst engaging in ERP tasks, participants will be encouraged to bring mindfulness skills to the tasks. In particular, this will involve an encouragement to bring mindfulness to intrusive thoughts as they arise (allowing thoughts to arise without suppressing them or becoming absorbed with them), to bring mindfulness to physical sensations of anxiety (noticing and accepting physical sensations of anxiety with curiosity and interest) and to bring mindfulness to urges to engage in compulsive behaviours (noticing compulsive urges and recognising there is a choice available - a choice to follow the urge and a choice to allow the urge to remain, without following it). Session 10 will focus on consolidating learning from the therapy and developing a therapy blueprint for continuing MB-ERP after the therapy has concluded. As with the standard ERP groups, therapy sessions will be audio recorded and rated by an expert to monitor and ensure therapy fidelity. This expert will provide regular supervision to the group facilitators. Additional supervision will be provided by an expert MBI therapist in order to ensure adherence to MBI principles and practice.

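### Read literally, the protocol has the blinded assessor conduct the Change Interview, which is likely to reveal the therapy received

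*Protocol article*

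**What the plan says.** Design and sample size describes the blinding as follows: "This is a pilot study for a single blind, prospective RCT". The same section sets the assessment times: "Measures will be taken at baseline (Time 1), post-therapy (Time 2) and at 6 months post-therapy (Time 3".

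Procedure gives baseline assessment to a first RA, before randomisation. It then states: "Post-group assessments on each of the outcome measures will be conducted by a second RA who will be blind to group allocation".

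The Change Interview is the last entry under Secondary outcome measures: "The Change Interview is a semi-structured questionnaire designed to ask participants their experiences of a psychological intervention". Within it, "participants are asked to comment on the aspects of the intervention that helped change to occur", and also on aspects that may have hindered change.

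Under Exposure and response prevention engagement, "participants will be asked to record in a daily diary the number of ERP tasks performed each day". In the MB-ERP arm the home mindfulness exercises go into the same record, "with practice being recorded in the daily diary".

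Data analysis estimates treatment effects on the primary outcomes at both follow-up times. It makes the application for definitive-trial funding depend on whether effects on Y-BOCS-II, sessions attended and ERP tasks completed favour MB-ERP.

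**The concern.** In a comparison of two group therapies, participants and facilitators know which therapy is being given. Blinding of the outcome assessor is therefore the protection available for any rating in which the assessor exercises judgement. The protocol names that assessor and then, through the wording of the assignment and the layout of the measures section, gives the same person an interview about the content of the therapy.

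An assessor who learns the allocation may rate differently, knowingly or not. The Background states that the team expects the mindfulness-based approach to do better, so a shift towards MB-ERP is the direction to guard against. The estimated effect is to feed the power calculation for the definitive trial, and the funding decision looks at the direction of effects without a numerical threshold. A modest bias could therefore carry forward. Blinding that has been lost cannot be restored at analysis.

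**Working it through.** **Step 1. Who is blind.** The trial is single blind (Design and sample size), and the only party described as blind is the second RA (Procedure).

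**Step 2. What that RA does.** The assignment covers every outcome measure after therapy. The Change Interview stands under the Secondary outcome measures heading. Taken together, the two places give the interview to the blinded RA. Nothing in the text shown exempts it, gives it to someone else or orders it after the ratings.

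**Step 3. Whether the interview reveals the arm.** The MB-ERP section describes a mindfulness practice and a 20-minute inquiry in sessions, an MP3 player for daily home practice, and a breathing exercise from session 6. The ERP section has none of these. A question about what helped or hindered invites an MB-ERP participant to name them. Data analysis also has the interviews analysed separately by condition to understand change in each therapy, so an interview that concealed the therapy would not serve its purpose.

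**Step 4. Which ratings would be affected.** This depends on two facts the article does not state.

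| Interview held | Rater at six months | Ratings no longer blind |
|---|---|---|
| Post-therapy, after the ratings | Same RA | Six-month Y-BOCS-II and MINI |
| Post-therapy, before the ratings | Same RA | Post-therapy and six-month |
| Post-therapy, before the ratings | Different RA | Post-therapy |
| Post-therapy, after the ratings | Different RA | None |
| Six months, after the ratings | Either | None |

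**Step 5. Size.** The documents give no figure for rater bias. The following only illustrates sensitivity.

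- Group sizes: 40 recruited gives 20 per arm. With 40% attrition, 20 × 0.60 = 12 per arm, which is the stated minimum (and 24 / 0.60 = 40 reproduces the recruitment target).
- Assumption: a bias of b SD towards MB-ERP, with b between 0.1 and 0.3, and no true effect. Baseline adjustment and clustering by therapy group are ignored.
- Formula: P(Y-BOCS-II estimate favours MB-ERP) = Φ(b / √(2/n)), with n per arm.

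| b (SD) | n = 20, √(2/20) = 0.316 | n = 12, √(2/12) = 0.408 |
|---|---|---|
| 0 | 50% | 50% |
| 0.1 | 62% | 60% |
| 0.2 | 74% | 69% |
| 0.3 | 83% | 77% |

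The column for 12 is the more relevant one if the effect is confined to six months and attrition reaches the planned maximum. The calculation concerns Y-BOCS-II alone.

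**The case against.** The article does not treat the Change Interview consistently as an outcome measure. The Abstract names depression, wellbeing and obsessive-compulsive beliefs as secondary outcomes and gives the interview a sentence of its own. The Background also separates it from the outcome and process measures, and Data analysis handles it by thematic analysis. The measure lists are used loosely elsewhere: the baseline assignment refers to all the measures described earlier, which cannot include an interview about change since therapy began. The authors may have meant only the scales. This stands, and it is why the point is limited to a literal reading held with moderate confidence. It does not remove the need to reword, because a reader who follows the text as printed would give the interview to the blinded RA.

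A reader might infer that the procedure is certain to break the blind before the six-month Y-BOCS-II. The documents do not support that. The timing of the interview is not stated, the participant flow figure is not available here, and the identity of the six-month rater is not given. An interview after the last rating is compatible with the text.

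A reader might also infer that the diaries unblind the assessor. Participants complete them during therapy, and nothing says that the blinded RA collects or reads them. They warrant a precaution and are not an error in the plan.

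The funding decision does not turn on Y-BOCS-II alone: sessions attended and ERP tasks completed also count, and neither is described as scored by a rater. If the ratings come first at the post-therapy visit, that estimate stays blind. Nor does the article state how Y-BOCS-II is administered, so the scope for rater bias rests on the assumption that the RA scores it.

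**Conclusion.** The concern holds in a limited form. As worded, Procedure and Secondary outcome measures together give the blinded assessor an interview that is likely to disclose the allocation, and this conflicts with the single-blind claim. The consequence for the ratings is conditional. Six-month ratings lose their blind if the interview is held post-therapy and the same RA rates at six months. Post-therapy ratings lose it if the interview comes before them.

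The size of any bias in the Y-BOCS-II effect is unknown. Under an assumed bias of 0.1 to 0.3 SD, the chance that a null effect looks favourable to MB-ERP rises from 50% to between 60% and 77% with 12 per arm, or between 62% and 83% with 20 per arm. Neither the amount nor the direction of bias comes from the documents, so these figures show sensitivity only.

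This should be fixed, with moderate confidence. It is not a demonstrated failure of blinding in a trial that, as a pilot, does not set out to show a significant difference.

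**What to change.** Amend the assignment in Procedure so that the blinded second RA conducts only the Y-BOCS-II, the MINI and the self-report questionnaires. Give the Change Interview to the first RA, whose baseline assessments precede randomisation and so cannot be affected by later knowledge of the arm. Alternatively, hold the interview only after the participant's last blinded rating. State when the interview takes place and who rates at six months.

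As a precaution, route the daily diaries away from the blinded RA, since those from the MB-ERP arm contain mindfulness entries, and record any unblinding that occurs.

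The cost is minor: some scheduling of a second staff member, or a change in the order of assessments. No extra post, measure or participant is needed. Recruitment was ongoing when the article was submitted, and the change protects only ratings made after it is in place.

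Suggested wording: *After therapy and at six months, the Y-BOCS-II, MINI and questionnaires will be administered by a second RA blind to allocation. The Change Interview will be conducted by a different RA, or after the final blinded rating. Diaries will not be available to the blinded RA, and any unblinding will be recorded.*
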